**Methods/Design:**

A randomized multi-center clinical trial comparing cost-effectiveness of open and laparoscopic repair of incisional hernias. Patients with a symptomatic incisional hernia, eligible for laparoscopic and open incisional hernia repair. Only surgeons, experienced in both open and laparoscopic incisional hernia repair, will participate in the INCH trial. During incisional hernia repair, a mesh is placed under or on top of the fascia, with a minimal overlap of 5 cm. Primary endpoint is length of hospital stay after an incisional hernia repair. Secondary endpoints are time to full recovery within three months after index surgery, post-operative complications, recurrences, mortality and quality of life.

Our hypothesis is that laparoscopic incisional hernia repair comes with a significant shorter hospital stay compared to open incisional hernia repair. A difference of two days is considered significant. One-hunderd-and-thirty-five patients are enrolled in each treatment arm. The economic evaluation will be performed from a societal perspective. Primary outcomes are costs per patient related to time-to-recovery and quality of life.

The main goal of the trial is to establish whether laparoscopic incisional hernia repair is superior to conventional open incisional hernia repair in terms of cost-effectiveness. This is measured through length of hospital stay and quality of life. Secondary endpoints are re-operation rate due to post-operative complications or recurrences, mortality and quality of life.

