**Figure 2 F2:**
[figure not shown]
Classification of incisional hernias according tot the European Hernia Society.

Postoperatively: open or laparoscopic/length of the scar/duration of surgery/type of mesh used/size of the mesh/type of mesh fixation/presence of bleeding/accidental bowel lesion/use of tubes/use of per-operative antibiotics/possible re-operation.

Inpatient: daily VAS score/use of analgesics/length of hospital stay/morbidity/mortality/QOL at two days post-surgery.

During Follow-up at 2 weeks and 3 months: healthcare and lost productivity costs/QOL at 2 weeks and 3 months post-surgery will be measured through the Short Form 36 and the Carolina Comfort Scale/time to return to work/recurrence/pain/wound infection/patient satisfaction/other morbidity.

During long-term follow-up at 1, 3 and 5 years: Recurrence/pain/wound infection/patient satisfaction/other morbidity.

**Primary outcomes** are:

Length of hospital stay. This is the time until discharge. A patient can be discharged when he/she is able to move normally, tolerate a normal diet and has a VAS painscore < 5 without the use of opiates.

Quality of life measures through SF-36 and CCS.

**Secondary endpoints** are:

Re-operation rate for recurrence or complications of the incisional hernia repair. The analysis will be continued after the cost-effectiveness study has ended, a longer follow-up is needed to examine the recurrence-rate.

28 days post surgery morbidity and mortality,

Total mean costs will be related to the following effect measures in the cost-effectiveness analyses:

1) Time to full recovery.

2) Quality-adjusted life-years (QALYs) based on the SF-36D
[11].

Intention to treat analysis will be performed. Blinding is impossible as the surgical difference is visible from the outside.

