### Statistics

*Sample size calculation*: This is a superiority design: Our hypothesis is that length of hospital stay is shorter after incisional hernia repair, and therefore the laparoscopic approach will be superior in terms of cost-effectiveness. Statistics are based on an average hospital stay of 2 days (SD 5) after laparoscopic repair
[8]. The outcome is considered superior if there is a difference in hospital stay of more than 2 days. Therefore, 135 patients in each treatment arm are needed (alpha 0,05/power 0,9)
[16]. Loss to follow-up may occur; we will therefore aim for an inclusion of 300 patients.

*Randomisation* will be performed through a computer-guided system. A stratified block-randomisation will be used per centre. The randomisation code will be noted on the patients file. Peritonitis carcinomatosa, unplanned surgical procedures for pathology that was not discovered during pre-operative analysis, absence of an incisional hernia are reasons for post-randomization exclusion.

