### Goal

The goal of the trial is to establish whether laparoscopic incisional hernia repair is superior to conventional open incisional hernia repair in terms of cost-effectiveness. This is measured through length of hospital stay and quality of life. Secondary endpoints are re-operation-rate (due to complications or recurrence), morbidity, mortality and shape of the abdomen.

In current surgical practice there is on going discussion about the possible benefits of laparoscopic incisional hernia surgery. Scientific evidence is lacking to determine whether laparoscopic correction is superior to conventional open techniques in terms of cost-effectiveness.

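### Quality of life is a primary outcome in the Methods but secondary in the Abstract, while hypothesis, alpha and power cover length of hospital stay only

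*Protocol article*

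**What the plan says.** The places that bear on this point in the protocol article are:

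- **Abstract, Methods/Design, endpoint statement:** "Primary endpoint is length of hospital stay after an incisional hernia repair". The next sentence makes quality of life secondary: "Secondary endpoints are time to full recovery within three months after index surgery, post-operative complications, recurrences, mortality and quality of life".
- **Abstract, Methods/Design, goal statement:** the main goal is cost-effectiveness, and "This is measured through length of hospital stay and quality of life". The sentence directly after it makes quality of life secondary again: "Secondary endpoints are re-operation rate due to post-operative complications or recurrences, mortality and quality of life".
- **Case record form, primary outcomes list:** length of hospital stay, then "Quality of life measures through SF-36 and CCS". The secondary list there does not contain quality of life.
- **Case record form, follow-up:** "QOL at 2 weeks and 3 months post-surgery will be measured through the Short Form 36 and the Carolina Comfort Scale". A quality-of-life record two days after surgery is also listed for inpatients.
- **Goal:** the same goal sentence as in the Abstract, followed by "Secondary endpoints are re-operation-rate (due to complications or recurrence), morbidity, mortality and shape of the abdomen". Quality of life is absent from this list.
- **Statistics:** the hypothesis and the superiority criterion (a difference of more than 2 days) are about hospital stay. "Therefore, 135 patients in each treatment arm are needed (alpha 0,05/power 0,9"; no effect size or standard deviation for quality of life is given.

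The Abstract also speaks of primary outcomes of the economic evaluation (costs related to time to recovery and quality of life). That is a separate use of the term and is not counted here.

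**The concern.** Which outcome is primary is protocol content, and the current text gives two answers. A reader of the Abstract would treat a quality-of-life result as secondary. A reader of the Case record form section would treat the same result as primary.

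The trial is unblinded, and the SF-36 and CCS are self-reported. Suppose length of stay shows no difference but a quality-of-life scale does. The Methods list would support calling that a primary result and the Abstract would deny it. The error rate and power in the Statistics section were set with only length of stay in view, so they say nothing about a claim resting on quality of life or on both outcomes together.

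**Working it through.** **1. The plan's own figure.** Inputs from the Statistics section: difference 2 days, SD 5 (given for the laparoscopic arm, taken as common to both), alpha 0.05, power 0.9. The number of sides is not stated.

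n per arm = 2 × (z₀.₉₇₅ + z₀.₉₀)² × SD² / difference² = 2 × (1.960 + 1.282)² × 25 / 4 ≈ 131.3, so 132. The t-test version gives 132.3, so 133. One-sided gives 108, which does not match. The stated 135 is therefore a two-sided calculation with slight rounding up.

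Power at 135 per arm: 2 / (5 × √(2/135)) = 3.286; 3.286 − 1.960 = 1.326; Φ(1.326) = 0.908 (0.906 by t test). With length of stay as the sole primary endpoint, both stated figures hold.

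**2. If success on either outcome were enough, each tested at 0.05 (assumed rule).**

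- Two independent tests: 1 − 0.95² = 0.0975.
- Two correlated tests (bivariate normal): 0.095, 0.091 and 0.070 at correlations 0.3, 0.5 and 0.9.
- Three independent tests (stay, SF-36, CCS, one score each): 1 − 0.95³ = 0.143.

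Power under this rule cannot fall below that of length of stay, because success on stay is already success. With stay at 0.90 and an independent quality-of-life test with no true effect, it is 1 − 0.10 × 0.95 = 0.905.

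**3. If both outcomes were required, each at 0.05 (assumed rule).** The chance of a false claim is at most 0.05, since a false claim needs a false positive on at least one of the two. Power, with stay at 0.90:

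| Assumed power for quality of life | Correlation 0 | Correlation 0.9 |
|---|---|---|
| 0.90 | 0.90 × 0.90 = 0.81 | 0.87 |
| 0.80 | 0.90 × 0.80 = 0.72 | 0.79 |

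**4. If alpha were split equally over two primaries.** At 0.025 each the critical value is 2.241. Length-of-stay power at 135 per arm is Φ(3.286 − 2.241) = 0.852, and 0.889 at 150 per arm. Restoring 0.90 needs 156 per arm, or 312 in total, against the planned inclusion of 300.

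The correlations and the quality-of-life power are assumptions, because the article gives no figures for them.

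**The case against.** The strongest reply is that the article does say what decides the trial. The Statistics section ties superiority to hospital stay, the Abstract gives one hypothesis and one primary endpoint, and the Time schedule section sets recruitment by the number needed for the difference in stay. No sentence says that a quality-of-life result alone suffices or that both are required. On that reading 0.05 and 0.9 both hold. This stands, and it is why the error rates above are conditional. It does not remove the conflict, because the Methods list still labels quality of life primary.

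A reader might infer more in four ways, and the documents do not support any of them.

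- **That the stated alpha and power both fail.** No single unadjusted rule loses both: either-or loses alpha and keeps power, and both-required keeps alpha and loses power.
- **That the error rate exceeds 20%.** Five tests (stay plus two instruments at two visits) would give 1 − 0.95⁵ = 0.226. That counts one score per instrument and makes every visit a separate, sufficient primary test, none of which is stated.
- **That quality of life is labelled primary throughout the body.** Only the list under Case record form uses that label. The goal statements say how the goal is measured, and in the Abstract that sentence is followed at once by quality of life as secondary. The Goal section is less clear, since its secondary list omits it.
- **That the lack of a named score, visit or multiplicity rule is itself an error.** An article commonly leaves these to the full protocol or analysis plan, which are not shown.

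**Conclusion.** The contradiction is real and sits in current text: quality of life is primary in one list and secondary in two others, and the goal statements lean towards a joint role. An analysis plan that is not shown could add a testing rule, but it could not make these passages agree. The finding is about endpoint status; the sample size calculation is sound for the outcome it addresses.

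The consequence depends on how the Methods list would be applied. Its size is a familywise error of roughly 0.07 to 0.0975 for two tests (0.143 for three independent tests) under an unadjusted either-or rule, or power of about 0.81 to 0.87 under a both-required rule with quality of life powered at 0.90. These figures rest on a common SD of 5, normal approximations, correlations from 0 to 0.9 for the two-test results, and decision rules that the article does not state. The conflict should be settled before results are known, because it determines what an unblinded trial may report as its primary result.

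**What to change.** Three wording changes:

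1. In the primary outcomes list under Case record form, name length of hospital stay as the only primary endpoint and move the SF-36 and CCS to the secondary list. Length of stay is the natural choice because it is the only outcome with a hypothesis, a criterion and a sample size.
2. Reword the goal statements in the Abstract and the Goal section so that they do not give quality of life equal standing with the primary endpoint. The Abstract's two secondary lists already contain quality of life and need no change on this point.
3. Add quality of life to the secondary list in the Goal section.

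If a confirmatory claim on quality of life is wanted, test it only after length of stay is significant at 0.05, with the score and visit named in advance. This fixed order keeps alpha at 0.05 and the length-of-stay power at about 0.91 with 135 per arm, with no extra patients.

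The cost is wording, plus one real concession: the trial gives up a primary claim on quality of life if length of stay fails. If that is not acceptable, the alternative is to keep both as primary and state the rule, accepting the loss of power or the larger sample shown above.

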### Economic evaluation

The aim of the economic evaluation is to describe the costs of laparoscopic and open repair of incisional hernias, and to relate the costs to the clinical effects of the treatments. The time horizon of the economic evaluation is 3 months. A societal perspective is chosen for this economic evaluation. For the measurement and valuation of the costs the Dutch costing guidelines will be used
[12].

#### Cost measurement and valuation

Health care utilization will be measured using hospital data and cost diaries during hospitalization and after 2 weeks and 3 months of follow-up. Health care costs include costs of the operation, hospital stay, medical supplies, additional examinations (CT, X-ray, laboratory, etcetera), medication, GP care, emergency visits and ambulatory hospital care. Absenteeism from paid and unpaid work and presenteeism at baseline and after 2 weeks and 3 months of follow-up will also be measured.

For the valuation of health care utilization standard prices published in the Dutch costing guidelines will be used
[12]. Medication use will be valued using prices of the Royal Dutch Society for Pharmacy. A detailed cost price calculation will be performed to estimate the costs of laparoscopic and open repair of incisional hernias.

### Analysis of cost-effectiveness

The analysis will be done according to the intention-to-treat principle. Missing cost and effect data will be imputed using multiple imputations according to the MICE algorithm developed by Van Buuren
[13]. Costs typically have a highly skewed distribution. Policy makers want to have information on the difference in mean total costs between the two treatment-groups to be able to estimate the total health care budget needed for a specific condition
[14]. Therefore, bias-corrected and accelerated bootstrapping with 5000 replications will be used to calculate 95% confidence intervals around the mean difference in total costs between the treatment groups. Incremental cost-effectiveness ratios (ICERs) will be calculated by dividing the difference in mean total costs between the treatment groups by the difference in mean effects between the treatment groups. Bootstrapping will be used to estimate the uncertainty surrounding the ICERs, which will be graphically presented on cost-effectiveness planes. Cost-effectiveness acceptability curves and net monetary benefits will also be calculated. Cost-effectiveness acceptability curves show the probability that collaborative care is cost-effective in comparison with usual care for a range of different ceiling ratios thereby showing decision uncertainty
[15].

The baseline data of both treatment groups will be described and 95% confidence intervals will be calculated. Additional as-treated analyses will be done, because patients who were planned to have a laparoscopic repair might have had an open correction and vice versa. Differences in primary and secondary endpoints between the two treatment groups will be calculated as well as their 95% confidence intervals. Student’s t tests, Chi square tests or Fisher exact tests will be applied where appropriate. The risk of re-operation will also be studied by application of a multiple logistic regression model.

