### Case record form

*At first presentation* in the outpatient clinics: age/sex/co-morbidity/pre-illness/working-social activities/surgical history/symptoms of the incisional hernia/classification of the incisional hernia:

The European Hernia Society (EHS) tried to categorize incisional hernias, in order to be able to compare different scientific incisional hernia research
[10]. A classification system of abdominal wall hernias was formulated (Figure 
2). This classification will be used in the INCH-trial.

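### The cost difference and ICER are defined as differences in group means with no covariate named, although baseline work loss is collected: a loss of precision, not a bias

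*Protocol article*

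**What the plan says.** All references are to the Protocol article.

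- **Perspective and horizon** (Economic evaluation): "A societal perspective is chosen for this economic evaluation", and "The time horizon of the economic evaluation is 3 months". Lost productivity therefore belongs to total costs; the Case record form section also lists it among the follow-up cost items.
- **Baseline measurement** (Cost measurement and valuation): "Absenteeism from paid and unpaid work and presenteeism at baseline and after 2 weeks and 3 months of follow-up will also be measured". The form completed at first presentation covers "age/sex/co-morbidity/pre-illness/working-social activities/surgical history/symptoms of the incisional hernia/classification of the incisional hernia", so working activities are also on record before surgery.
- **Cost contrast** (Analysis of cost-effectiveness): "bias-corrected and accelerated bootstrapping with 5000 replications will be used to calculate 95% confidence intervals around the mean difference in total costs between the treatment" arms. The ICER is obtained by "dividing the difference in mean total costs between the treatment groups by the difference in mean effects between the treatment groups". Neither definition names a covariate.
- **Stated use of baseline data** (same section): "The baseline data of both treatment groups will be described and 95% confidence intervals will be calculated". The only regression model named there is a logistic model for re-operation.
- **Randomisation** (Statistics): in blocks, stratified by centre. Work status is not a stratum.

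**The concern.** A patient without paid work cannot incur paid-work loss in either arm, and a patient already off work before surgery may well stay off work afterwards. Part of the between-patient variance in societal costs is therefore fixed before randomisation. The Background section suggests that the cohort mixes workers and non-workers: mean age at repair is 58 (SD 15), employment chances are reduced, and most patients are expected to return to work.

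The trial collects the variables that could remove this variance, but the estimator as defined does not call on them. Cost-effectiveness is the declared goal of the trial, while the sample size is set on length of stay alone and no precision is planned for costs. What is at stake is the width of the cost interval and the spread of the points on the cost-effectiveness plane. The acceptability curve and the net monetary benefit inherit that uncertainty.

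**Working it through.** **1. The plan's own figure.** The only sample size given is for length of stay: difference 2 days, SD 5, alpha 0.05, power 0.90.

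n per arm = 2 × (1.960 + 1.2816)² × 5² / 2² = 2 × 10.507 × 6.25 = 131.3, so 132 (133 with the t distribution; both two-sided).

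The stated 135 agrees within 3% and gives power 0.908. The target of 300 equals 270 / 0.90. These figures hold but say nothing about costs. The document gives no cost SD, no share of patients in work and no correlation between baseline work loss and total costs, so what follows uses assumed ranges.

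**2. Precision gain from adjustment.** Let r be the (multiple) correlation of the baseline work variables with total costs. Then SE(adjusted) / SE(crude) = √(1 − r²), and the crude sample size with the same precision is 135 / (1 − r²) per arm.

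| r (assumed) | SE ratio | SE reduction | Equivalent crude n per arm |
|---|---|---|---|
| 0.1 | √0.99 = 0.995 | 0.5% | 136 |
| 0.3 | √0.91 = 0.954 | 5% | 148 |
| 0.5 | √0.75 = 0.866 | 13% | 180 |

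**3. Chance imbalance in work status.** With working share p, the 95% range of the difference between arms is ±1.96 × √(2p(1 − p)/135).

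- p = 0.3: 1.96 × 0.056 = 0.109
- p = 0.5: 1.96 × 0.061 = 0.119
- p = 0.6: 1.96 × 0.060 = 0.117

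Shares of patients in work could thus differ between arms by 11 to 12 percentage points by chance. This is ordinary sampling variation, and the bootstrap interval for the crude difference already reflects it.

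**4. Bias and coverage.** An illustrative simulation used 135 per arm, no true difference, skewed costs and 4000 runs per scenario. Working share was 0.3 or 0.5, and baseline and follow-up work loss among workers correlated 0.3 or 0.5 on the log scale. Mean follow-up productivity cost per worker was exp(8.32) / exp(8.48) = 0.85 times the other costs.

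- SE ratios, adjusted to crude, were 0.889, 0.863, 0.886 and 0.862: a reduction of 11 to 14%.
- Neither estimator showed material bias. The largest mean estimate, 21.9, is 4% of its SD of 535.7.
- Coverage of 95% intervals was 94 to 95% for both. The intervals were normal-theory ones, not BCa.

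Since 1 − 0.889² = 0.21 and 1 − 0.862² = 0.26, these scenarios correspond to r of about 0.46 to 0.51. They sit at the favourable end of the table because of the assumed weight of productivity costs.

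**The case against.** The strongest objection is that the article never calls the cost comparison unadjusted. A bootstrapped mean difference can come from a regression, this is a condensed journal article, and covariates for an economic model are often left to a fuller document. That stands in part: a reader might infer that the plan has committed to an unadjusted analysis or ruled out baseline variables, and the document supports neither. It does not exclude them from the imputation model either. But the section is not silent on the estimator. It fixes the imputation algorithm, the bootstrap type and number of replications, and the ICER formula, and it names a regression where one is wanted. Taken at its word, the contrast is a difference in group means.

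A second objection is that nothing is invalid. This stands in full. A reader might infer that an imbalance in work status would bias the cost difference or the ICER. Under randomisation it does not: it is chance error that the interval already carries.

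A third is that the size rests on assumptions. This also stands. One could turn the SE ratio into power: a cost difference with 80% crude power would have Φ(2.802/√(1 − r²) − 1.96), which is 83.6% at r = 0.3 and 89.9% at r = 0.5. But the plan claims no power for costs, so these figures correspond to nothing planned. Total costs also include the operation, hospital stay, medication and other care, and nothing in the document supports a high r. Nor does the age distribution measure work status.

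Finally, adjusting only the cost side would leave an adjusted numerator over a crude denominator. The fix has to cover both.

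**Conclusion.** The point holds as an efficiency improvement of low severity. As written, the cost contrast and the ICER numerator are differences in group mean total costs with no named covariate, while relevant baseline variables are collected and given no stated role beyond description. The estimator is unbiased and its interval valid. The cost is precision: an SE about 0.5%, 5% or 13% larger than necessary, expressed as the reduction available at r = 0.1, 0.3 or 0.5. Those correlations are assumed, and at the low end the gain is negligible. The conclusion also assumes that paid-work status can be read from the working activities recorded at first presentation.

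**What to change.** In Analysis of cost-effectiveness, pre-specify the following.

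1. Estimate the difference in mean total costs by linear regression on the euro scale, with treatment, baseline productivity loss (absenteeism and presenteeism) and baseline paid-work status as covariates. The target remains a difference in mean costs, as the plan wants for budget decisions.
2. Bootstrap costs and effects jointly by resampling patients, with the planned 5000 replications. Estimate the effect difference in the same bootstrap under a consistent covariate approach, so that both parts of the ICER are treated alike.
3. Carry the adjusted cost difference into the ICER, the cost-effectiveness plane, the acceptability curve and the net monetary benefit.
4. Include the same baseline variables in the MICE model.
5. Report the crude difference as supportive.

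Fixing this in advance also removes any choice about adjustment after an imbalance has been seen.

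The cost is analysis-plan wording and a regression inside the bootstrap already planned, with no new data, visits or patients. There are two small downsides. Missing baseline items must be imputed. Baseline work loss must also be valued on the same basis as follow-up, and the article gives neither the valuation of productivity loss nor the baseline recall period, so both should be stated.

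### The SF-36 and CCS comparisons are given only simple two-group tests, which ignore the repeated visits and centre, and the planned imputation does not clearly reach them

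*Protocol article*

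**What the plan says.** - **Outcome.** The Case record form section (text after Figure 2) lists among the primary outcomes "Quality of life measures through SF-36 and CCS".
- **Timing.** The same section states "QOL at 2 weeks and 3 months post-surgery will be measured through the Short Form 36 and the Carolina Comfort Scale". The inpatient items also include "QOL at two days post-surgery", with no instrument named.
- **Tests.** The second paragraph of Analysis of cost-effectiveness covers all endpoints: "Differences in primary and secondary endpoints between the two treatment groups will be calculated as well as their 95% confidence intervals". The tests follow: "t tests, Chi square tests or Fisher exact tests will be applied where appropriate". No test is assigned to a particular endpoint, visit or analysis set.
- **Missing data.** The first paragraph of that section says "Missing cost and effect data will be imputed using multiple imputations according to the MICE algorithm". The Case record form section names two effect measures for the cost-effectiveness analyses: time to full recovery, and QALYs from the SF-36D.
- **Expected loss.** The Statistics section says "Loss to follow-up may occur; we will therefore aim for an inclusion of 300 patients". It also says that randomisation is blocked and stratified by centre.
- **Principle.** The Case record form section says "Intention to treat analysis will be performed", and Analysis of cost-effectiveness opens with the same principle.

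**The concern.** A t test takes one value per patient. It cannot use a 2-week score to inform a missing 3-month score, and it takes no account of centre although centre is a stratification factor. Used on unimputed data, it drops every patient without the form in question.

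The imputation sentence may or may not repair this. Read with the two named effect measures, it covers the SF-36 as an ingredient of the QALY but not clearly as a score, and it does not cover CCS. The same SF-36 forms could then be completed by imputation for the QALY and left incomplete for the score comparison. Enrolling 300 instead of 270 restores the number of patients but does not make those who return forms comparable between arms.

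The article says that blinding is impossible, so form return could depend on both recovery and arm. At stake is the quality-of-life difference, one of the two measures through which the Goal section says the aim is assessed. It could be shifted modestly in either direction, and would be estimated less precisely than the collected data allow.

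**Working it through.** **1. The plan's own figures.** Inputs from Statistics: difference 2 days, SD 5, alpha 0.05, power 0.90.

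n per arm = 2 × (1.960 + 1.282)² × (5/2)² = 2 × 10.51 × 6.25 ≈ 131.3, so 132 (133 with the t distribution). The stated 135 is within 3% of this. A one-sided test would give 108, so the plan is two-sided.

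The target of 300 equals 270/(1 − 0.10), an implied loss of 10%. These figures concern length of stay. No sample-size figure is given for SF-36 or CCS, so the 10% is the only indication of how many forms might be missing.

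**2. Detectable difference for a score.** At 135 per arm, 90% power and two-sided 0.05: (1.960 + 1.282) × √(2/135) = 3.242 × 0.1217 ≈ 0.39 SD (0.40 with the t distribution).

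**3. Simple bias formula for an observed-forms t test.** Assume 150 per arm and a fraction m missing in both arms. Assume also that non-returners differ from returners by d SD in one arm only. The full mean in that arm then differs from the returners' mean by m × d, which is the bias. With SE = √(2/(150(1 − m))), the two-sided type I error is Φ(−1.96 − bias/SE) + 1 − Φ(1.96 − bias/SE). The d values are assumptions.

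| Missing m | d = 0.25 | d = 0.5 | d = 1.0 |
|---|---|---|---|
| 5% | bias 0.0125, error 0.051 | 0.025, 0.055 | 0.05, 0.071 |
| 10% | 0.025, 0.055 | 0.05, 0.070 | 0.10, 0.130 |
| 20% | 0.05, 0.067 | 0.10, 0.121 | 0.20, 0.341 |

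With d = 0 the bias is 0 and the error is 0.05.

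**4. Simulation with a recovery-driven mechanism.** Assumptions, none from the article: no true difference at 3 months, 0.3 SD difference at 2 weeks, correlation 0.5 to 0.7 between visits, and 3-month missingness logistic in the 2-week score. Slopes are given as (laparoscopic, open).

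- Mechanism differs by arm, slopes (0, 1) and (−1, 1): absolute bias 0.05 to 0.13 SD at 10% missing and 0.09 to 0.24 SD at 20%. At 5% missing it is 0.02 to 0.07 SD.
- Same mechanism in both arms, slopes (1, 1): bias about 0.
- Using the 2-week score by regression: residual 0.003 SD or less in every case.

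At 10% missing the bias is 0.05/0.39 ≈ 13% to 0.13/0.39 ≈ 33% of the detectable difference. The small residual shows only that the remedy works when missingness depends on the observed 2-week score, because the simulation was built that way.

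**5. Precision.** The gain from modelling both visits and centre was not calculated. The article gives no correlation between visits and no between-centre variance for these scores.

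**The case against.** A reader might infer that the scores will be tested visit by visit on returned forms only, so that the quality-of-life result is not intention-to-treat. The article does not support this. It says neither that the tests are run per visit nor that imputed data are kept out of them. Its list of tests is generic, and a t test can be run on multiply imputed data. Intention to treat is stated twice, once in the same section as the tests. Missing forms alone do not make an analysis by randomised arm depart from it.

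Other points on that side:

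- **Effect data may include quality of life.** The Abstract and Goal section say that cost-effectiveness is measured through length of stay and quality of life. On that reading the SF-36 score is already imputed. This stands as a possible reading, but it competes with the explicit list of two effect measures, and CCS is still not named.
- **This is analysis-plan detail in a condensed article.** That holds for the exact model and analysis set, and silence on them is not the point. The article does, however, name a method for these endpoints, and a better one is available from data it already collects.
- **The bias figures rest on assumptions.** This stands. They need a mechanism that differs by arm, and the upper values need slopes of opposite sign.
- **The stakes are limited.** The Abstract calls quality of life secondary, and the sample size rests on length of stay, which does not depend on returned forms. This also stands, although the Case record form section lists quality of life as primary.

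**Conclusion.** The concern holds in a limited form. For outcomes listed as primary and measured repeatedly, the article names only tests that use neither the repeated measurements nor the centre stratification. Its imputation rule does not clearly reach the SF-36 score comparison and does not name CCS.

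The consequence is conditional. If the tests use observed forms, and if form return depends on recovery differently in the two arms, the bias at the implied 10% loss is about 0.05 to 0.13 SD under the assumed mechanisms, against a detectable difference of about 0.39 SD. It is near 0 if the mechanism is the same in both arms. There is also some unquantified loss of precision. This should be improved, but it is not an error that invalidates the trial.

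**What to change.** In Analysis of cost-effectiveness, replace the generic tests for SF-36 and CCS scores with one of the following, by randomised arm:

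- **Mixed model.** A repeated-measures model with arm, visit (2 weeks, 3 months), arm-by-visit interaction, centre and unstructured covariance, reporting the arm difference with its 95% confidence interval at each visit. The 2-week score enters as a response, not as a covariate for the 3-month comparison. State whether the 2-day measurement is included and with which instrument. Patients with no form at all contribute nothing to this model.
- **Imputed datasets.** Analyse the scores in the MICE datasets already planned, extended to CCS and including all randomised patients. This also aligns the SF-36 score comparison with the QALY.

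Keep the observed-data t test as a sensitivity analysis.

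The cost is a few sentences of text and a little analysis work, with no new data. The downside is reliance on missing-at-random given the observed scores. That is a weaker assumption than an observed-forms t test needs, but it does not remove bias from missingness that depends on unobserved recovery.
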